### Demographic Information Analysis

For each group, continuous data yielded the mean, SD, median, minimum, maximum, and 95% CIs, whereas categorical data yielded frequencies and percentages. To compare groups, we used a two-sample *t* test or Wilcoxon rank-sum test for continuous data, and a chi-square test or Fisher’s exact test for categorical data. Baseline information that was recognized as significantly different between the 2 groups was considered a covariate in the efficacy analysis to correct for heterogeneity between the treatment groups.

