### Randomization, Blinding, and Allocation Concealment

A total of 236 participants who met the criteria were assigned to the HH333 or control group at a ratio of 1:1 by a statistician independent of this clinical study, using the block randomization method with R 4.4.0 (Comprehensive R Archive Network). Patients and investigators will be blinded to prevent access to the allocation results. Patients will be blinded to the study medication they are administered because they are taking either the treatment medication or a placebo. The treatment medication and placebo will be identical in size, shape, and appearance and packaged in the same type of packaging.

For allocation concealment, an independent statistician who generates the random numbers delivers a randomization code to each clinical trial site in a sealed, impermeable envelope. The investigators at each site will open the randomization envelopes in sequence in front of the patients to assign participants, and the open envelopes will be kept separate.

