### Sample Size

In previous studies, ischemic stroke recurrence rates of 12.5%-12.8% over 24 months with conventional antiplatelet therapy (aspirin or dipyridamole) [22] and 1.7% over the same period with HH333 [19] were reported. Therefore, the sample size was 106 patients per group and 212 patients in total at 2 years with a control group (P_2_=0.125-0.128), HH333 group (P_1_=0.017), a significance level (α) of 5% and a target power of 80%. Finally, a dropout rate of 10% was considered, resulting in a sample size of 118 patients per group for a total of 236 patients.

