### Statistical Analysis

All statistical analyses were two-sided with a 5% significance level. The statistical program SAS (version 9.4 or more, SAS Institute) was used for the analysis. If at any point there are missing values or participants are dropped before the end of the study, the data will be treated as missing data. All data obtained from the participants were analyzed in 3 forms: full analysis set, per-protocol set, and safety set. Efficacy analysis will be conducted using the results of the full analysis set as the main analysis, and a per-protocol set analysis will be conducted separately to evaluate whether there are differences from the full analysis set results. Safety analysis was performed on the safety set and the safety of the study medications was evaluated. The full analysis set includes all data from participants with at least one efficacy assessment at the primary outcome after taking the study medication. The per-protocol set included participants who were eligible for full analysis and successfully completed the study. The safety set included all data from participants who received at least one dose of the study medication.

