### Efficacy Analysis

#### Analysis of Primary Efficacy Endpoints

The number of events will be presented for ischemic stroke recurrence during the 2-year study medication treatment period, the odds ratio of stroke recurrence will be calculated, and logistic regression analysis will be performed with ischemic stroke recurrence as the dependent variable and other factors such as HH333 treatment, risk factors, and neurological deficits as independent variables.

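### Baseline variables that differ significantly between arms are added to an open covariate list, so the primary logistic model depends on chance in a trial expecting about 15 events

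*Protocol article*

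**What the plan says.** Under Demographic Information Analysis, the arms are compared at baseline with a t test or "Wilcoxon rank-sum test for continuous data, and a chi-square test" or Fisher's test. The next sentence sets the rule: "Baseline information that was recognized as significantly different between the 2 groups was considered a covariate in the efficacy analysis", with the stated aim "to correct for heterogeneity between the treatment groups". No threshold is given there, but the Statistical Analysis section says "All statistical analyses were two-sided with a 5% significance level".

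Under Analysis of Primary Efficacy Endpoints, the primary analysis is a logistic regression of ischemic stroke recurrence with "other factors such as HH333 treatment, risk factors, and neurological deficits as independent variables". Neither the risk factors nor the deficit measure is named, and the wording leaves the list open. The article does not say how this list and the baseline-difference rule combine. Since the rule refers to the efficacy analysis without exception, it reaches the primary model.

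Under Randomization, Blinding, and Allocation Concealment, participants are allocated 1:1 by block randomisation.

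**The concern.** When arms are formed by randomisation, a significant baseline difference is a chance event. It says nothing about whether the variable predicts recurrence. A rule based on the p-value admits irrelevant variables as readily as prognostic ones, and it does not add a strong predictor whose imbalance falls short of significance.

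Two consequences follow. First, the covariate set cannot be known until the baseline data have been compared by group. The odds ratio is non-collapsible, meaning that its value changes with the covariates in the model even without confounding. The quantity estimated therefore shifts with the randomisation draw. Second, the design expects few events, so even one or two extra terms matter. What is at stake is whether the primary result comes from a model that was fixed in advance.

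**Working it through.** **Step 1: the plan's own sample size.** Inputs from Sample Size: P1 = 0.017, P2 = 0.125 (lower end of the stated range), two-sided 5%, power 80%.

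- Pooled proportion = (0.017 + 0.125)/2 = 0.071; difference d = 0.108.
- Uncorrected n = [1.96 × √(2 × 0.071 × 0.929) + 0.842 × √(0.017 × 0.983 + 0.125 × 0.875)]² / 0.108² = 87.6, so 88.
- With continuity correction: n/4 × [1 + √(1 + 4/(n × d))]² = 105.3, so 106 per group.
- Dropout: 106/0.90 = 117.8, so 118 per group.

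The stated 106 and 118 per group reproduce.

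**Step 2: expected events at these rates.**

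- 212 patients: 106 × (0.017 + 0.125) = 15.1 (15.4 with P2 = 0.128).
- 236 patients: 118 × 0.142 = 16.8 (17.1 with P2 = 0.128).
- HH333 arm alone: 106 × 0.017 = 1.8, or 118 × 0.017 = 2.0.

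**Step 3: how often chance selects a covariate.** Each null test selects with probability 0.05. With k independent tests, P(at least one) = 1 − 0.95^k and the expected number is 0.05k.

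| k | P(at least one) | Expected number |
|---|---|---|
| 4 | 19% | 0.2 |
| 10 | 40% | 0.5 |
| 20 | 64% | 1.0 |

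The number tested is not stated, so k is an assumption. Four matches the demographic items in the footnotes to Table 1 (age, sex, smoking, alcohol). Twenty is those four plus the 16 blood items listed there (5 blood count, 11 biochemistry). Blood items are correlated, so the larger figures are approximate.

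**Step 4: effect on power and error.** Logistic simulation with 106 per arm, a 12.5% control rate, 4,000 runs per scenario and one prognostic covariate whose strength (log odds ratio per SD) is assumed. The design rates imply an odds ratio of (0.017/0.983)/(0.125/0.875) = 0.12. An odds ratio of 0.35 is an assumed weaker effect.

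| Treatment OR | Prognostic log-OR | Unadjusted | Adjust only if significantly imbalanced | Always adjust | Forgone by the rule (points) |
|---|---|---|---|---|---|
| 0.12 | 0.7 | 73.7% | 73.9% | 74.2% | 0.3 |
| 0.12 | 1.2 | 75.8% | 76.1% | 78.4% | 2.3 |
| 0.35 | 0.7 | 46.2% | 46.5% | 48.2% | 1.7 |
| 0.35 | 1.2 | 41.9% | 42.1% | 46.9% | 4.7 |

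The last column is taken from unrounded values. Under the null, rejection was 3.9% to 4.7% for all three approaches. The covariate was selected in 4.5% to 5.5% of runs, which confirms the 5% in Step 3.

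**The case against.** The strongest reply is that the primary model does not rest on the baseline-difference rule. The primary endpoint section enters risk factors and neurological deficits whatever the baseline table shows, and the rule can only add terms to them. That stands. A reader might infer that the model depends on chance imbalance instead of prognosis; the article does not support this.

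It follows that the last column in Step 4 mostly measures adjusting against not adjusting. If the planned risk factors include the main predictor, the loss due to the rule is smaller still. A reader might also infer an inflated false-positive rate or a serious loss of power, and the simulation shows neither.

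A reader might further infer that the model is picked with knowledge of treatment or outcome. The article gives no timing for the comparisons, masked group labels would suffice for them, and the rule looks at baseline data only. The model would still depend on the data.

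It can be said, too, that adjusting for an imbalanced predictor removes bias in that particular sample. This is true of a predictor, but a significance test does not identify predictors, and a fixed prognostic adjustment does the same work for the variables that it covers.

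Finally, exact covariate names are commonly left to an analysis plan, which is not shown. Their absence is not the point made here. The selection rule is stated, and an analysis plan faithful to it would carry it forward.

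**Conclusion.** The point holds in a limited form. The article fixes a rule that adds chance-selected terms to an unnamed prognostic list, and it does not reconcile the two. With about 15 to 17 events expected in total and about 2 on HH333, the primary model and its odds ratio depend on the randomisation draw.

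The rule brings no material gain over no adjustment: at most 0.4 percentage points in the four scenarios, which is negligible. Against planned adjustment it forgoes about 0.3 to 5 points. Type I error is unaffected. The harm is a model that is not fixed in advance, more than lost power.

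The event counts rest on the design rates. The selection frequencies rest on an assumed number of independent tests, and the power figures on assumed prognostic strengths and one covariate. The shift in the odds ratio through non-collapsibility follows in principle but has not been quantified. The change is worth making because it is nearly free.

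**What to change.** Delete the sentence under Demographic Information Analysis that selects covariates by significance, and present the baseline table descriptively. Under Analysis of Primary Efficacy Endpoints, replace the open list with one or two prognostic covariates already collected, fixed before unblinding and used whatever the baseline table shows. Baseline K-NIHSS is an example, possibly with stroke history; Table 1 schedules both.

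The list must stay very short. Treatment plus two single-term covariates makes three slopes, or about 15/3 = 5 events per slope. Hospital indicators should not be added to this sparse primary model. The independent statistician "delivers a randomization code to each clinical trial site in a sealed, impermeable envelope", which may suggest a separate sequence per site, but stratification by site is not stated. Two indicators for three hospitals would bring the model to five slopes, about 15/5 = 3 events each.

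The cost is about two sentences, with no new data and no change to the sample size. The Results section reports that no data analysis has been conducted, so the change can be made cleanly. The small downside is that a chance imbalance in an unlisted variable would be handled only in a sensitivity analysis.

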### Efficacy Analysis

#### Analysis of Primary Efficacy Endpoints

The number of events will be presented for ischemic stroke recurrence during the 2-year study medication treatment period, the odds ratio of stroke recurrence will be calculated, and logistic regression analysis will be performed with ischemic stroke recurrence as the dependent variable and other factors such as HH333 treatment, risk factors, and neurological deficits as independent variables.

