Specifically, HH333 inhibits the progression of microangiopathy, a key factor in small-vessel disease, and thus prevents the recurrence of ischemic stroke induced by small-vessel disease with a 2-year recurrence rate was 1.12%-2.02% [18-20], which is less than conventional antiplatelet agents [21-24]. Regarding safety, a previous retrospective study showed that the incidence of adverse events with HH333 was 2.0%, with no serious adverse events (SAEs) [25]. However, since these studies were all single-arm retrospective observational studies, there is no comparative analysis with a control group, and the data rely on medical records, which can be inaccurate. Therefore, there is a need for prospective clinical studies with a control group to rationalize and better understand these findings.

We present a protocol for a randomized controlled clinical trial to validate the clinical efficacy and safety of HH333 in patients with ischemic stroke induced by small-vessel disease. This study aimed to provide a high level of evidence for the efficacy of HH333 in ischemic stroke and ultimately propose a novel alternative for stroke treatment.

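### The planned logistic regression is not specified for very few events: at the plan's own rates about 1 trial in 6 has no HH333 recurrence and no finite log odds ratio, and the power depends on a test that is not named

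*Protocol article*

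**What the plan says.** Under Analysis of Primary Efficacy Endpoints, the number of recurrences over the 2-year treatment period is to be presented; then "the odds ratio of stroke recurrence will be calculated, and logistic regression analysis will be performed". HH333 treatment, risk factors and neurological deficits are the independent variables. The section names no test statistic or interval method, and says nothing about an arm without events. Demographic Information Analysis adds as covariates any baseline variables found to differ significantly between groups. Chi-square and Fisher tests are mentioned only for baseline comparisons and adverse events.

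Under Sample Size, the inputs are two proportions: 0.017 for HH333 and 0.125 to 0.128 for control, with "a significance level (α) of 5% and a target power of 80" percent. The result is that "the sample size was 106 patients per group and 212 patients in total at 2 years". Then "a dropout rate of 10% was considered, resulting in a sample size of 118 patients per group for a total of 236 patients". The formula is not named. Statistical Analysis adds: "All statistical analyses were two-sided with a 5% significance level".

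The Introduction reports earlier HH333 studies in which the "2-year recurrence rate was 1.12%-2.02" percent.

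**The concern.** The protocol fixes a logistic model and an odds ratio as the primary analysis, while its own assumptions put about two events in the HH333 arm. Ordinary maximum likelihood is unreliable there. If the HH333 arm has no event, the treatment coefficient runs off to minus infinity, its standard error is meaningless, and a Wald p-value will not reach significance however large the difference. A clear success for HH333 could then leave the planned analysis without a usable estimate or interval.

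The sample size also appears to come from a different test from the one planned, so the 80% target does not describe the logistic model. If the handling of a zero cell is chosen after the counts are known, the primary p-value depends on a choice made with the data in view.

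**Working it through.** **Inputs.** Two-sided 5% level (Statistical Analysis). HH333 rate 0.017, control rate 0.125 to 0.128, target power 80%, 106 per group before and 118 after 10% dropout (Sample Size). HH333 range 1.12% to 2.02% (Introduction).

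**1. Reproduce the plan's figure.** With p̄ = (0.125 + 0.017)/2 = 0.071 and difference 0.108:

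n₀ = [1.960·√(2·0.071·0.929) + 0.842·√(0.125·0.875 + 0.017·0.983)]² / 0.108² = 87.6

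With the continuity correction: n = (n₀/4)·[1 + √(1 + 4/(n₀·0.108))]² = 105.3, rounded up to 106. This matches exactly.

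Dropout: 106/0.90 = 117.8, rounded up to 118. This also matches.

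None of the other variants tried gives 106 at a control rate of 12.5%: without the correction 88, unpooled variance about 85, arcsine about 74, one-sided with correction 87. A log-odds-ratio (Wald) formula would need about 121 to 122 evaluable per group.

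**2. Expected events at 106 per group.** HH333: 106 × 0.017 = 1.8. Control: 106 × 0.125 = 13.25. Total: about 15.

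**3. Chance of no HH333 event**, (1 − p)ⁿ:

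| HH333 rate | n per group | Chance |
|---|---|---|
| 1.7% | 106 | 0.983^106 = 16.2% |
| 1.7% | 118 | 0.983^118 = 13.2% |
| 1.12% | 106 | 0.9888^106 = 30.3% |
| 2.02% | 106 | 0.9798^106 = 11.5% |

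In these trials the sample odds ratio (HH333 to control) is 0 and its logarithm is not finite.

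**4. Example: 0 versus 13 of 106.** Fisher's exact test gives p = 0.0002. The likelihood-ratio statistic is 2·[13·ln(13/106) + 93·ln(93/106) − 13·ln(13/212) − 199·ln(199/212)] = 18.9 on 1 degree of freedom, far beyond 3.84. The Wald statistic is not usable.

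**5. Exact power.** All pairs of independent binomial counts were enumerated for a treatment-only model at a two-sided 5% level. Trials with an empty arm count as non-significant for Wald. HH333 rate 1.7%:

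| Test | n = 106, control 12.5% | n = 106, control 12.8% | n = 118, control 12.5% | n = 118, control 12.8% |
|---|---|---|---|---|
| Logistic, Wald | 72.8% | 74.1% | 79.5% | 80.4% |
| Logistic, likelihood ratio | 92.6% | 93.5% | 94.9% | 95.5% |
| Pearson chi-square | 91.3% | 92.4% | 94.2% | 95.0% |
| Fisher | 86.2% | 87.7% | 89.2% | 90.5% |

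Firth-penalised likelihood ratio at 106 per group and control 12.5%: 91.0%. Its type I error with 12.5% in both arms is 4.8%.

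Among trials with at least one event in each arm, Wald power at 106 (control 12.5%) is 86.9%. The shortfall therefore comes mainly from the zero-event trials.

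**The case against.** The protocol never names the Wald test. Within the same logistic model the likelihood-ratio test has 92.6% power, and every alternative computed exceeds 80%. Sizing on two proportions and then analysing by logistic regression is common practice, and 80% is called a target, not the power of the logistic model. The choice of test statistic and the handling of zero cells are often left to an analysis plan, which is not shown. All of this stands, and it rules out saying flatly that the trial has 73% power or is underpowered.

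The figure of 106 is also the low end. The full analysis set takes anyone with one post-dose primary assessment, so the analysed number could lie anywhere between 106 and 118. At 118 the Wald test is essentially at target. This stands too, although the plan itself budgets for 10% dropout and treats dropouts' data as missing.

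A reader might infer that a better drug always means lower Wald power. That is not so. At 106 per group and control 12.5%, Wald power is 58.9% at an HH333 rate of 4%, 69.9% at 3%, 74.3% at 2.02%, 72.8% at 1.7% and 63.7% at 1.12%. It falls only below about 2%.

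A reader might also infer a strict limit of one or two covariates. The protocol lists no specific covariates, so no such number can be derived from it.

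What the objection does not remove is the zero cell. It follows from the stated model and the stated rates, whichever p-value is used: the maximum-likelihood log odds ratio has no finite value in 16.2% of trials at 106 per group and 13.2% at 118.

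**Conclusion.** The point holds as a should-fix. At the plan's own rates the stated analysis yields no finite log odds ratio in roughly 1 trial in 6 (106 per group) to 1 in 7.6 (118 per group), and in 30.3% of trials at 106 per group if the HH333 rate is 1.12%. The sample size matches a continuity-corrected two-proportion calculation, so the 80% does not describe the logistic model. Power within that model is about 73% or about 93% at 106 per group, depending on an unstated choice between Wald and likelihood ratio; Wald rises to about 80% at 118.

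The assumptions are these. The logistic regression is ordinary maximum likelihood. The power figures are for treatment alone, since the covariates are not listed. The sample size formula is inferred from the exact match. The documents do not support concluding that the trial is too small: the defect lies in the analysis specification and the power statement.

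**What to change.** In Analysis of Primary Efficacy Endpoints, specify Firth-penalised logistic regression with a profile-likelihood test and confidence interval for the treatment effect. A likelihood-ratio or exact test with a matching interval would also serve. Name a short covariate list in advance, in view of about 15 expected events.

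In Sample Size, state which test the 80% refers to and give the power of the test actually used, at 106 and at 118 evaluable per group.

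The cost is one sentence and a restated power figure. No extra patients are needed, and the Firth method is available in the SAS software already planned. The Results section reports 12 patients randomized and no data analysis, so the change can still be made before any outcome data are examined.

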Experiment medication administration		✓	✓	✓	✓	✓	✓	✓	✓	✓	✓		
Medication adherence^i^			✓	✓	✓	✓	✓	✓	✓	✓	✓		If needed
Concomitant treatment		✓	✓	✓	✓	✓	✓	✓	✓	✓	✓	✓	If needed
Primary efficacy endpoint: recurrence of ischemic stroke			✓	✓	✓	✓	✓	✓	✓	✓	✓	✓	If needed
Secondary efficacy endpoints^j^		✓		✓	✓	✓	✓	✓	✓	✓	✓		If needed
Exploratory endpoints^k^		✓		✓	✓	✓	✓	✓	✓	✓	✓		If needed
Safety assessments^l^			✓	✓	✓	✓	✓	✓	✓	✓	✓		If needed
Adverse events^m^		✓	✓	✓	✓	✓	✓	✓	✓	✓	✓	✓	

^a^Telephone investigation.

^b^UV: Unscheduled visit. Visiting on a day other than the original visit schedule due to an adverse event, etc.

^c^Screening performed within 14 days of informed consent.

^d^Age, sex, smoking, and alcohol history.

^e^Within 1 year prior to visit 0.

^f^Time of first onset and diagnosis (including year, month, and day if possible), date of computed tomography or magnetic resonance imaging, ischemic stroke territory, Trial of Org 10172 in Acute Stroke Treatment classification, history of stroke-related surgery, stroke risk factors, and stroke-related symptoms.

^g^Within 4 weeks prior to visit 0.

^h^Complete blood count (red blood cell, hemoglobin, hematocrit, platelet, white blood cell); biochemistry (fasting blood glucose, blood urea nitrogen, creatinine, natrium, potassium, chloride, aspartate aminotransferase, alanine aminotransferase, C-reactive protein, calcium, uric acid); urine human chorionic gonadotropin for women of childbearing age, excluding sterilization and menopause (more than 12 months since last menstrual period); premature menopause before the age of 40 years, follicle-stimulating hormone test for differential diagnosis.

^i^Drop out if <80%.

^j^Total scores of Fatigue Severity Scale (FSS), Fatigue Assessment Scale (FAS), Korean Patient Health Questionnaire (K-PHQ-9), and probability of each type of Pattern Identification (fire heat, dampness-phlegm, Qi deficiency, and Yin deficiency).

^k^Total scores of the Korean National Institutes of Health Stroke Scale (K-NIHSS), Korean modified Rankin Scale (K-mRS), Korean modified Barthel Index (K-mBI), Korean Montreal Cognitive Assessment (K-MoCA).

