Most patients with stroke have a multimorbidity status due to various risk factors such as high blood pressure, diabetes, and hyperlipidemia, and controlling risk factors is crucial, making them susceptible to polypharmacy [48]. In a study of the Scottish general population, patients with stroke were more than twice as likely to have multimorbidity compared to patients without stroke, with 12.6% of patients with stroke taking 11 or more medications compared to only 1.5% of patients without stroke [49]. Patients with stroke taking more than 5 or 6 medications are at increased risk for adverse events and falls [50,51], which can severely impact rehabilitation outcomes [48]. Since HH333 has effects on improving stroke risk factors [17], it is expected to complement or replace stroke risk factor therapies, thereby reducing medication use.

Although most herbal medicines are safe and rarely cause liver and kidney injury, some herbal medicines occasionally cause liver injury, and *Scutellariae radix*, a component herbal medicine of HH333, is the main causal herbal medicine responsible for herb-induced liver injury with about 1% of incidence [52]. However, there have been no studies on the dose-dependent toxicity of *Scutellariae radix*, but previous *in vivo* studies have reported no toxicity at a dose of 2000 mg/kg [53,54], which is a much higher dose than the *Scutellariae radix* dose of HH333. In addition, in a 656-patient safety study, no liver or kidney injury was reported with HH333, and mild adverse events of gastrointestinal symptoms, headache, insomnia, chest discomfort, fatigue, and thirst occurred in 2% of patients, with no SAEs [25]. No adverse events were reported in 771 patients in a retrospective cohort study of HH333 published to date [18-20,55]. Therefore, HH333 is expected to be safe with no adverse events, including liver or kidney injury.

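### The primary logistic model adjusts for several risk factors and neurological deficits when only about 15 to 17 recurrences are expected, so the HH333 odds ratio is likely to be unstable and, if HH333 works, pushed away from 1.

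*Protocol article*

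**What the plan says.** In the protocol article, Analysis of Primary Efficacy Endpoints promises event counts, an odds ratio, and a logistic regression of recurrence on "other factors such as HH333 treatment, risk factors, and neurological deficits as independent variables". The covariates are plural but are neither listed nor counted. Demographic Information Analysis adds to the efficacy analysis any baseline item that differs significantly between the arms.

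Candidate factors appear elsewhere:
- Table 1, footnote d (Study Design) collects "Age, sex, smoking, and alcohol history".
- Footnote f collects stroke risk factors without naming them.
- K-NIHSS is measured on day 0.
- The Discussion refers to "various risk factors such as high blood pressure, diabetes, and hyperlipidemia".

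Sample Size assumes "ischemic stroke recurrence rates of 12.5%-12.8% over 24 months with conventional antiplatelet therapy" and 1.7% on HH333, with "a significance level (α) of 5% and a target power of 80" per cent. That gives 106 evaluable patients per group, or 118 after allowing for 10% dropout. Statistical Analysis adds: "All statistical analyses were two-sided with a 5% significance level".

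**The concern.** An ordinary logistic regression is fitted by maximum likelihood. With few events per coefficient, its estimates become unstable and tend to lie further from 1 than the truth. Here the smaller outcome class is the recurrences, and almost all of them are expected in one arm. If HH333 is effective, each extra covariate tends to make the adjusted odds ratio look more favourable than it should.

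At stake are the size and stability of the efficacy estimate, and whether there is a usable estimate at all if no HH333 patient has a recurrence.

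**Working it through.** **1. Reproduce the plan's sample size.** Inputs from Sample Size and Statistical Analysis: 12.5% v 1.7%, two-sided 5%, 80% power, 1:1. The mean rate is 0.071 and the difference is 0.108.

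n = [1.960 × √(2 × 0.071 × 0.929) + 0.842 × √(0.125 × 0.875 + 0.017 × 0.983)]² / 0.108² = 87.6, so 88 without continuity correction.

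With continuity correction: (87.6/4) × [1 + √(1 + 4/(87.6 × 0.108))]² = 105.3, so 106. Then 106/0.9 = 117.8, so 118. Both stated figures reproduce.

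**2. Expected recurrences.**
- 212 evaluable: 106 × (0.017 + 0.125) = 15.1; with 12.8% in control, 15.4.
- All 236 followed: 118 × 0.142 = 16.8; with 12.8%, 17.1.
- HH333 arm: 106 × 0.017 = 1.8, or 118 × 0.017 = 2.0.

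**3. Events per slope at 15 events** (treatment counts as one slope).
- Two covariates: 15/3 = 5.0.
- Four: 15/5 = 3.0.
- Eight: 15/9 = 1.7.

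The eight are age, sex, smoking, alcohol, hypertension, diabetes, hyperlipidaemia and a neurological score. The article collects or names these, but does not say that they are the model's covariates.

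**4. Chance of no HH333 event.** 0.983^106 = 16%; 0.983^118 = 13%. The maximum-likelihood odds ratio is then not finite, even with no covariate.

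**5. Simulated odds ratio at the planned rates, 106 per arm.** The unadjusted true value is (0.017/0.983)/(0.125/0.875) = 0.121. With prognostic covariates the conditional value is slightly lower. Entries are medians over all trials, including those with no HH333 event. The covariate settings are assumptions.

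| Covariates | A | B | C | D |
|---|---|---|---|---|
| 0 | 0.108 v 0.121 (11% low) | 0.117 v 0.117 | 0.117 v 0.121 (3%) | – |
| 2 | 0.107 v 0.120 (11%) | 0.110 v 0.117 (6%) | 0.111 v 0.121 (8%) | 0.106 (9–12%) |
| 4 | 0.102 v 0.119 (14%) | 0.105 v 0.117 (10%) | – | – |
| 8 | 0.094 v 0.117 (20%) | 0.091 v 0.117 (22%) | 0.102 v 0.121 (16%) | 0.091–0.095 (21–22%) |

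- A: binary, prevalence 0.4, log odds ratio 0.4; 2,000 trials.
- B: binary, log odds ratio 0.4; one true value for all rows.
- C: binary, no prognostic effect; 2,000 trials.
- D: prevalences 30–65%, log odds ratio 0 or 0.2 per SD; 2,500–4,000 trials; true value 0.116–0.121.

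**6. The same question with non-finite fits dropped.** The geometric mean odds ratio against the true value (1,500 trials; prevalence 0.4, log odds ratio 0.4) was:
- no covariates: 0.131 v 0.121
- two: 0.127 v 0.120
- four: 0.117 v 0.119
- seven: 0.119 v 0.117
- ten: 0.102 v 0.115 (11% low)

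Dropping those fits removes about 16% of trials, which are the most extreme in HH333's favour.

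**7. Other scenarios.**
- 12.5% v an assumed 7%, eight covariates: median 3% to 5% low.
- No effect, 12.5% in both arms, up to ten covariates: odds ratio 0.99 to 1.02, type I error 4.1% to 6.7%.
- No effect, 7.1% in both arms, eight covariates: type I error 4.3% to 6.6%, depending on the test and the covariate assumptions.

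**8. Firth-penalised fit, settings of step 6.** With two covariates the mean log odds ratio was −2.09 against a true −2.12, that is 0.124 v 0.120. The median was −1.964, or 0.140. With seven covariates the mean was −2.091 against −2.144, or 0.124 v 0.117.

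**The case against.** A reader might infer that the model enters every risk factor and that the HH333 odds ratio is therefore exaggerated. The article supports neither. Its list is illustrative, the number of covariates is unknown, and Results says that no data have been analysed. It also does not say whether the odds ratio it will calculate is crude or adjusted.

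The article is condensed, so an unnamed covariate list could fairly be left to an analysis plan. That stands, and the missing list is not the point here. The point is the stated choice to put plural risk factors and neurological deficits into the primary model at the event count its own rates imply.

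The size of the effect can also be contested. Part of the shift comes from trials with no HH333 event and is present with no covariates (0% to 11% in step 5). Among finite fits there is little exaggeration up to seven covariates. The standard error of the log odds ratio is about 0.8, so a shift of 16% to 22% (0.17 to 0.25 on the log scale) is under a third of it. Wald 95% coverage with eight covariates was 97%. All of this stands, and it limits the concern to the size and stability of the estimate.

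It would also be wrong to infer a built-in bias towards HH333. Under no effect there is none, and if HH333 were harmful the same mechanism would magnify the harm.

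**Conclusion.** The concern holds in a limited form. The event count is firm on the plan's own rates: about 15 to 17 recurrences, about 2 of them on HH333. That is too few for a primary model with more than one or two covariates.

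If HH333 works as planned, the median adjusted odds ratio is expected to be about 6% to 11% too low with two covariates (up to 12% in one setting of D), 10% to 14% with four and 16% to 22% with eight. These figures rest on maximum-likelihood fitting, on the assumed covariate distributions and on counting trials with no HH333 event. The four- and eight-covariate figures also rest on a model size that the article does not state. The shift shrinks to a few per cent at 12.5% v 7%. With no effect there is no systematic bias, and at 7.1% or 12.5% in both arms there is little inflation of type I error.

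The 13% to 16% chance of no finite estimate depends only on the planned HH333 rate and the sample size, and limiting the covariates does not remove it.

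**What to change.** Restrict the primary model to HH333 treatment plus at most two baseline covariates named in advance and already collected, for example age and day-0 K-NIHSS. State that this model's treatment odds ratio is the primary result, and do not add covariates to it on the strength of baseline significance tests. Fit it by Firth-penalised or exact logistic regression, so that an HH333 arm without events still gives a usable result. Report the wider risk-factor model as a labelled exploratory analysis.

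The cost is analysis wording only; no new data are needed and none have been analysed. Fewer prognostic factors are adjusted for in the primary result, and risk-factor odds ratios become exploratory. Firth estimates lean towards 1: slightly on the mean log scale (0.124 v 0.120 with two covariates), but more in the median (0.140), so the penalty should be stated alongside the estimate.
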